**Supplementary Figure S1: Flow diagram summarizing the process of the trial**

Identify patient with post-stroke depression

Check eligibility

Consent

**Collect baseline data**: physical exam, vital signs, computerized cognitive tests, questionnaires, psychiatric assessment, blood samples.

Start treatment with 300 mg/day Maraviroc

**Follow-up assessment on week 2 and weeks 4, 7, and 10:** physical exam, vital signs, computerized cognitive tests (at week 10), questionnaires, psychiatric assessment, record of AEs related or not related to the medication assignment, concomitant medications, pill counts, blood samples.

**Telephone contact assessment on weeks 3, 5, 8, and 9:** record of AEs, and concomitant medications.

**Follow-up assessment on weeks 14, and 18 (post-treatment assessments):** physical exam, vital signs, questionnaires, psychiatric assessment.

Supplemental Methods: Sample size calculation

The percentage of pilot study participants who tolerate a new treatment or the proportion of eligible patients who provide informed consent for participation would be representative of the tolerance or participation rates if all potential participants were studied. Providing a means to estimate these quantities enables early indicators of treatment tolerability and enrollment feasibility.

Weight gain and sexual dysfunction are well documented with the current anti-depressants, usually selective serotonin reuptake inhibitors (SSRIs) or Serotonin-Norepinephrine Reuptake Inhibitors (SNRIs). Another side effect of SSRIs is hyponatremia, which can limit their use in stroke patients.

It is of clinical interest to identify augmentative therapies that can alleviate some of the known side effects affecting a high percentage of patients receiving SSRIs or SNRIs (an average of 30% of people treated with an SSRI reported sexual dysfunction^1^, while 25% of individuals had a significant body weight increase^2^ and an average of 22% had hyponatremia^3^). Therefore, it is desirable to rule out potential treatments not consistent with this rate of sexual dysfunction, weight gain, and hyponatremia before considering more conclusive testing. Using the following equation,

**
[figure not shown]
**

(where π is the probability of the adverse event of interest)

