we would conclude that the augmentative therapy has sexual dysfunction rates less than 0.31, at the 90% confidence level, if a total of 10 patients are recruited and all 10 do not experience sexual dysfunction. We would conclude that the augmentative therapy has weight gain rates less than 0.25, at the 90% confidence level, if a total of 8 patients are recruited and all 8 do not experience weight gain. We would conclude that the augmentative therapy has hyponatremia rates less than 0.22, at the 90% confidence level, if a total of 9 patients are recruited and all 9 do not experience weight gain. Therefore, an initial sample size of 10 patients would be sufficient to identify augmentative therapies, such as Maraviroc. The results of such a pilot study could then be used to rank-order Maraviroc as a potential therapy thereby proving an empirically justified approach to therapy development.

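### The sizing section says 10 patients suffice to identify a better-tolerated add-on, but its zero-event rules do not make such a drug likely to pass, and two printed bounds do not match the stated 90% confidence

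*Protocol*

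**What the plan says.** Under Supplemental Methods: Sample size calculation, the protocol takes reference rates for three antidepressant side effects from the literature: "an average of 30% of people treated with an SSRI reported sexual dysfunction", "25% of individuals had a significant body weight increase" and "an average of 22% had hyponatremia". It gives the aim as a screen: "it is desirable to rule out potential treatments not consistent with this rate of sexual dysfunction, weight gain, and hyponatremia".

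It then gives one zero-event rule per side effect:

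- Sexual dysfunction: "sexual dysfunction rates less than 0.31, at the 90% confidence level, if a total of 10 patients are recruited", with none of the 10 affected.
- Weight gain: "weight gain rates less than 0.25, at the 90% confidence level, if a total of 8 patients are recruited", with none of the 8 affected.
- Hyponatremia: a rate below 0.22 at 90% confidence if none of 9 is affected. The sentence names weight gain as the event, apparently a copying slip.

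The section concludes: "Therefore, an initial sample size of 10 patients would be sufficient to identify augmentative therapies, such as Maraviroc". It adds that the results could be used to rank Maraviroc as a candidate. It gives no expected event rate under Maraviroc, no probability of seeing zero events, and no reading of one or more events.

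**The concern.** The conclusion does not follow from the rules. A 90% zero-event bound limits the chance of seeing no events when the true rate is at the reference level. A claim that 10 patients are enough to identify a better-tolerated drug concerns something else: the chance that such a drug shows no events. The section never addresses that chance, and with 10 patients it is modest unless the true rate is very low.

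The bounds themselves can also be checked, and two of the three do not agree with the stated confidence level.

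What is at stake is how the pilot's tolerability counts are read. Someone relying on this section could take one event in 10 as evidence against Maraviroc, when that result settles nothing. They could also quote a bound for 0/10 that is looser than the data support at the stated confidence.

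**Working it through.** **Inputs, all from the sample size section.** Reference rates 0.30, 0.25 and 0.22; printed bounds 0.31, 0.25 and 0.22; printed n of 10, 8 and 9; confidence 90%; trial size 10. The equation is a figure that is not shown, so I assume the exact zero-event form and try both one-sided and two-sided readings.

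**1. The plan's own figures.** With 0 events in n, the one-sided 90% upper limit is 1 − 0.10^(1/n). The n needed to exclude a rate π is ln(0.10)/ln(1 − π).

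| Event | Printed | One-sided 90% | Two-sided 90% | Two-sided 95% |
|---|---|---|---|---|
| Sexual dysfunction, 0/10 | 0.31 | 0.206 | 0.259 | 0.308 |
| Weight gain, 0/8 | 0.25 | 0.250 | 0.312 | 0.369 |
| Hyponatremia, 0/9 | 0.22 | 0.226 | 0.283 | 0.336 |

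The two-sided columns use 0.05 and 0.025 in place of 0.10. Weight gain reproduces at one-sided 90%. Hyponatremia nearly does, but 0.226 is not below 0.22: the required n is 9.27, so 10 patients. The sexual dysfunction bound fits neither 90% reading; 0.31 matches a two-sided 95% limit. No single confidence level reproduces all three lines. At one-sided 90% the required n is 6.46 for 0.30, 8.004 for 0.25 and 9.27 for 0.22, so a total of 10 is still reached, through hyponatremia.

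**2. What the rules control.** P(zero events) = (1 − p)^n. At the reference rates: 0.70^10 = 2.8%, 0.75^8 = 10.0%, 0.78^9 = 10.7%. This is the chance that a drug no better than the reference passes.

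**3. What the conclusion needs.** The same formula at lower true rates. The fractions of the reference are illustrative.

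| True rate | Sexual dysfunction, n = 10 | Weight gain, n = 8 | Hyponatremia, n = 9 |
|---|---|---|---|
| Half | 0.85^10 = 19.7% | 0.875^8 = 34.4% | 0.89^9 = 35.0% |
| One quarter | 0.925^10 = 45.9% | 0.9375^8 = 59.7% | 0.945^9 = 60.1% |
| One tenth | 0.97^10 = 73.7% | 0.975^8 = 81.7% | 0.978^9 = 81.9% |

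With all 10 enrolled patients counted for each event, the half-rate row becomes 19.7%, 0.875^10 = 26.3% and 0.89^10 = 31.2%. For an 80% chance of 0/10, the true rate must be no more than 1 − 0.8^(1/10) = 2.2%.

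**4. One or more events.** Exact (Clopper-Pearson) one-sided 90% upper limits for 10 patients are 0.206 (0 events), 0.337 (1) and 0.450 (2). One event gives a limit above 0.31, 0.25 and 0.22, so it does not show a rate below any reference. The one-sided 90% lower limit for 1/10 is 1 − 0.9^(1/10) = 0.010, so it does not show a high rate either.

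**The case against.** The best defence is that this is a pilot with an initial sample size, ahead of more conclusive testing, and that a pilot need not be powered. The numbers 8, 9 and 10 can be read as minimum sizes per event, with the largest adopted. The rules say only what would be concluded from zero events and attach no failure to one event. Half the reference rate is an outside assumption, and at one tenth the chance of passing is fairly good. All of this stands. It limits the point to the printed conclusion and the printed bounds; it does not rescue either.

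Three stronger readings are tempting but not supported:

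- **All three rules must be passed, so the three chances should be multiplied.** The section speaks of relieving some of the side effects, states three separate conditionals and never requires all of them. A joint figure would also need an assumption about dependence between events. Only the per-event figures are used here.
- **The 8- and 9-patient rules could be met by any 8 or 9 of the 10 enrolled, inflating the false-pass rate.** The text rules this out. The weight gain rule applies "if a total of 8 patients are recruited and all 8 do not experience weight gain", so 8 is the whole sample, and the hyponatremia rule is built the same way.
- **This screen decides whether Maraviroc goes forward.** The Design section ties further research to the drug proving safe. The primary safety endpoint is the absence of serious treatment-emergent adverse events and of those leading to discontinuation, which is not defined by these three events. Ranking is offered only as a possible use.

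**Conclusion.** The point holds in a limited form. The zero-event rules bound a rate if no event is seen; they do not support the claim that 10 patients suffice to identify a better-tolerated add-on. Per event, the chance of passing is about 20% to 35% at half the reference rates, 46% to 60% at one quarter and 74% to 82% at one tenth. These figures rest on the exact binomial model and on assumed true rates, because the protocol states none.

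Separately, the 0.31 bound for 0/10 does not match 90% confidence on either reading (0.206 or 0.259), and 0/9 does not give a rate below 0.22 (0.226 at one-sided 90%). The sidedness is assumed because the equation is not shown, but no choice of sidedness at 90% reproduces the 0.31.

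The total of 10 is not in question, and neither the primary safety endpoint nor its analysis is affected.

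**What to change.** Rewrite the one paragraph:

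- Replace the three rules with the limits that the 10 enrolled patients give, the same for each event, and state that they are one-sided 90% exact limits: 0.206 for 0/10, 0.337 for 1/10, 0.450 for 2/10. This also removes the 0.31 and 0/9 errors and the slip that names weight gain in the hyponatremia rule.
- State that 0/10 supports a rate below each reference (0.206 is below 0.22, 0.25 and 0.30) and that 1 or a few events in 10 is inconclusive. The sidedness must be explicit: the two-sided 90% limit of 0.259 would be below 0.30 but not below 0.25 or 0.22.
- Give the chance of 0/10 at plausible true rates: 0.95^10 = 60% at 5%, 0.90^10 = 35% at 10%, 0.85^10 = 20% at 15%.
- Remove the claims that 10 patients suffice to identify Maraviroc and that the results could rank it.

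No change in sample size is needed. The only cost is that the stated justification for 10 patients becomes less favourable.

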# We plan to perform a proof-of-concept open label add-on clinical trial of 300 mg Maraviroc given once daily for 10 weeks in 10 patients with PSD. Depression scores over time will serve as outcome measures and each patient function will be compared before and after treatment with study drug, beyond current treatment with other anti-depressants, such that the efficacy will be analyzed only beyond the efficacy of current treatments. The study will consist of 3 phases: (1) screening, (2) open-label treatment (weeks 1-10), and (3) post-treatment follow-up (8 weeks). The primary objective will be safety and tolerability of Maraviroc 300 mg per day in subjects with PSD. If proved safe, we plan continued research to establish efficacy using different dosages of Maraviroc

Objectives

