### Interventions

Participants will be outpatients diagnosed with PSD up to 12 months after the index event. Following baseline assessments, all participants will receive the active treatment - Maraviroc 300 mg once daily for 10 weeks in an open-label design. They will be followed for another 8 weeks after cessation of Maraviroc. The study intervention will be given as add-on therapy to the patient’s usual prescribed care (treatment as usual),thus all participants will continue their existing antidepressant treatment without change. All participants will be instructed to continue their usual treatment for the whole trial duration. Endpoints:

Primary Safety Endpoint: No serious treatment-emergent adverse events (TEAEs), no TEAEs leading to discontinuation.

Primary Efficacy Endpoint: The primary efficacy evaluation will be the MADRS total score as measured by the change from baseline (i.e., Day 1 pre-dose) to Week 10.

Secondary Endpoints: • Proportion of responders • Proportion of subjects in remission • Change from baseline to week 10 in subject-reported depressive symptoms using the QIDS-SR16. • Change from baseline to week 10 in severity of illness using the CGI-S and CGI-I. • Change from baseline to week 10 in severity of illness using the PGI-S and PGI-C. • Change from baseline to week 10 in anxiety symptoms, as measured by the GAD-7. • Change from baseline to week 10 in the SIS, ADL, and RNL scores.

Neuroimaging acquisition and processing A magnet resonance imaging (MRI) protocol will be performed before visit 1 and will consist of previously described pulse sequences ^36^. All axial slices will be prescribed on the same orientation, covering the whole brain, aligned along the fourth ventricle-orbitofrontal orientation. MRI analyses will include assessment of white matter (WM) hyperintensities, tissue segmentation and Brain atrophy measures as we have previously described^36^.

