**Prohibitions and Restrictions**

- Potent CYP3A4 inhibitors are not permitted within 1 week or within a period less than 5 times the drug’s half-life, whichever is longer, before the first dose of study medication and throughout the study.
- Potent CYP3A4 inducers are not permitted for 30 days prior to the first dose of study medication and throughout the study.

Safety Evaluations

Physical examination, body weight, vital signs, 12-lead ECG, clinical laboratory tests, and evaluation of adverse events and concomitant therapies will be performed throughout the study to monitor subject safety. Suicidal ideation and behavior will be assessed by a psychiatrist, as well as continuous follow-up of mental state and adverse events after cessation of Maraviroc treatment.

Primary Efficacy Measures:

**MADRS** -The 10-item clinician-administered MADRS was designed to be used in subjects with MDD to measure the overall severity of depressive symptoms (Montgomery and Asberg 1979). The MADRS has been validated, is reliable, and is acceptable to regulatory health authorities as a primary scale to determine efficacy in major depression. The structured interview guide for the Montgomery Asberg Depression Rating Scale (SIGMA) will be used for each administration (Williams 2008). Using structured interview guides have previously been shown to increase the reliability of given scales. In depression, ‘response’ is commonly defined as a ≥50% reduction in the initial symptom score and remission is typically defined as a total score of ≤10 (Montgomery 1994). The primary efficacy evaluation will be the change from baseline in the MADRS total score in the treatment phase.

Secondary Efficacy measures:

**QIDS-SR16** - The patient administered 16-item quick inventory of depressive symptoms- self report (QIDS-SR16) is designed to be used in patients with MDD to measure the overall severity of depressive symptoms (Rush 2003; Trivedi 2004).

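### The justification of n = 10 rests on zero counts of three antidepressant side effects that are not the primary endpoint and that depend on which antidepressants the patients take

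*Protocol*

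**What the plan says.** In the protocol, Supplemental Methods: Sample size calculation takes three benchmark rates from the antidepressant literature: "an average of 30% of people treated with an SSRI reported sexual dysfunction", "25% of individuals had a significant body weight increase", and 22% for hyponatremia. It then states three zero-event rules at 90% confidence: 10 patients against 0.31 for sexual dysfunction, 8 against 0.25 for weight gain, and 9 against 0.22 for hyponatremia. It concludes: "Therefore, an initial sample size of 10 patients would be sufficient to identify augmentative therapies, such as Maraviroc". It adds that the results could be used to rank Maraviroc as a candidate therapy.

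Other sections describe a trial that does not match this rule:

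- **Primary safety endpoint** (Methods, Endpoints): "No serious treatment-emergent adverse events (TEAEs), no TEAEs leading to discontinuation". None of the three sizing events is named.
- **Background treatment** (Methods, Interventions): "all participants will continue their existing antidepressant treatment without change". Screening and Baseline assessments admits patients with or without an antidepressant, and requires a dose unchanged for at least 2 months in those who take one.
- **Safety Evaluations**: "Physical examination, body weight, vital signs, 12-lead ECG, clinical laboratory tests, and evaluation of adverse events and concomitant therapies". Body weight and chemistry have rows in Table S1. Sexual function has neither a row nor an instrument.
- **Design**: "If proved safe, we plan continued research to establish efficacy using different dosages of Maraviroc".

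**The concern.** A zero-event rule is informative when three things hold: the event is the one the trial has to judge, the benchmark is the rate expected without the property being tested, and the event is looked for in every patient. Here the first two fail, and the third is not shown for sexual dysfunction.

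The benchmarks are rates on SSRIs/SNRIs, but Maraviroc is added to whatever the patient already takes, including nothing. In a patient on an SSRI, an event may come from the SSRI. In a patient on none, the comparison no longer concerns augmentation. The same count can therefore arise from a different recruitment mix with no change in what Maraviroc does.

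At stake is what may be claimed afterwards. The protocol says that ten patients can identify Maraviroc as an augmentative therapy, and it makes further research conditional on safety having been proved. It gives no figure for what ten patients can show about serious TEAEs or TEAEs leading to discontinuation.

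**Working it through.** **1. The plan's own figure.** The equation is an image that is not shown. I assume the exact zero-event rule, (1 − π)^n ≤ 0.10, so n = ln(0.10)/ln(1 − π).

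- π = 0.31: n = 6.21, so 7. The plan says 10.
- π = 0.25: n = 8.004, so 9. The plan says 8, which gives 89.99% confidence.
- π = 0.22: n = 9.27, so 10. The plan says 9, which gives 89.3% confidence. Its wording here repeats weight gain; I read it as hyponatremia.

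The largest requirement is 10, so the overall n reproduces. The pairing of 10 patients with 0.31 does not. At one-sided 90% the bound for 0/10 is 1 − 0.10^(1/10) = 0.206, and 0.31 matches the two-sided 95% bound, 1 − 0.025^(1/10) = 0.308. The problem below is the rationale, not the total of 10.

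**2. Dependence on the antidepressant mix.** Inputs are the plan's rates of 30%, 25% and 22%. Let k of the ten patients take an antidepressant. Assume that Maraviroc adds no events, that patients are independent, that any event present on treatment counts, and that patients without an antidepressant have no events. Then P(0/10) = (1 − rate)^k.

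| k of 10 on an antidepressant | Sexual dysfunction, 0.70^k | Weight gain, 0.75^k | Hyponatremia, 0.78^k |
|---|---|---|---|
| 10 | 2.8% | 5.6% | 8.3% |
| 4 | 24% | 32% | 37% |
| 0 | 100% | 100% | 100% |

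The same inert add-on passes with a probability anywhere from 2.8% to 100%, and the protocol does not fix k.

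**3. Dependence on the counting rule.** Background doses have been stable for at least 2 months, so side effects may already be present on Day 1. If only events new or worsened from Day 1 count, those drop out. The 30/25/22% rates are then no longer the rates to compare with, and a zero count does not show improvement on an SSRI. The sizing text does not say which count is meant.

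**4. The primary endpoint by the same logic.** For 0/10 patients with a serious TEAE or a TEAE leading to discontinuation:

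- one-sided 90%: 1 − 0.10^(1/10) = 20.6%
- one-sided 95%: 1 − 0.05^(1/10) = 25.9%

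The chance of observing 0/10 is 0.95^10 = 60% at a true rate of 5%, 0.90^10 = 35% at 10%, and 0.80^10 = 11% at 20%. A clean result is thus compatible with rates that matter clinically, and the protocol does not say so.

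**The case against.** The strongest defence is the stated aim. The sample size section looks for add-ons that relieve known SSRI/SNRI side effects. Under that aim a neutral add-on should not pass, so a low chance of 0/10 with everyone on an SSRI is the screen working as intended. This stands as far as it goes: a reader might infer that the rule wrongly fails a harmless drug almost every time, and the documents do not support that. It holds only with all ten on antidepressants at the full rates and with existing events counted. The protocol also attaches no stopping or no-go consequence to a non-zero count. But the aim would need every patient to be on an SSRI/SNRI with side effects recorded at baseline. The eligibility text does not require this, and no objective or endpoint mentions relief of side effects. With four of ten on antidepressants an inert add-on passes 24% to 37% of the time, so the rule does not work as that screen either.

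Three other stronger readings should be set aside.

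- **That sexual dysfunction would be counted only if volunteered.** The Safety Plan includes events found through staff questioning, and the later Interventions section has weekly calls with a standard script and checklist. The checklist's content is not shown, so all that can be said is that systematic asking is not documented.
- **That the weight benchmark is a ten-year rate.** This rests on a reference title, "Antidepressant utilisation and incidence of weight gain during 10 years". Whether the 25% is a ten-year figure cannot be checked from the protocol.
- **That the comparison is empty in patients without an antidepressant.** A low rate there would show that Maraviroc does not itself produce these events as often as an SSRI. That is a fair finding, though not one about augmentation.

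It is also fair to say that this is a proof-of-concept trial. The point does not ask for more patients, only that the claim fit what ten can show.

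**Conclusion.** The concern holds as a mismatch between rationale and design. The number 10 is justified on events outside the primary endpoint, against rates that belong to the background drugs, in a population whose antidepressant use is not fixed. For a Maraviroc that adds nothing, the chance of a zero count runs from 2.8%, 5.6% and 8.3% to 100% depending on the mix. The statements that ten patients suffice to identify augmentative therapies, or to rank Maraviroc among them, are therefore not supported.

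A reader might infer that the trial cannot say anything about tolerability. That goes too far: TEAEs, weight, laboratory tests and vital signs are still collected and summarised. What ten patients offer on the primary endpoint is modest and should be stated: with no events, a true rate above 20.6% (one-sided 90%) or 25.9% (one-sided 95%) is excluded.

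The figures rest on the assumed form of the missing equation, on independent patients, on the plan's own benchmark rates and, for the four-of-ten row, on an assumed event-free remainder. The bounds on the primary endpoint need only the ten patients, independence and the exact binomial rule.

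**What to change.** - Keep n = 10. Remove the comparison with SSRI/SNRI rates and the sentences on identifying and ranking Maraviroc.
- Justify n on the primary safety endpoint: if none of 10 patients has a serious TEAE or a TEAE leading to discontinuation, a true rate above 20.6% (one-sided 90%) or 25.9% (one-sided 95%) is excluded. Choose one level and use it throughout.
- In Design, replace the clause that makes later research conditional on proof of safety with that statement.
- Report sexual dysfunction, weight gain and hyponatremia descriptively, as events new or worsened from Day 1, listed by antidepressant use at baseline. List rather than test: 0/5 in a subgroup would give a one-sided 95% bound of 1 − 0.05^(1/5) = 45%.
- Either add a sexual-function item to the existing scripted checklist from Day 1, or delete the sexual-dysfunction claim.

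The cost is a rewording, at most one checklist item, and a more modest stated conclusion. Sample size and visit schedule do not change.
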